**5.2 Inclusion/Exclusion Criteria**

**Research participants** include women living in IDP camps in Leogane, Haiti. The participants will be recruited by trained peer health workers (PHW), NEGES community development agency and other community organizations serving women in Leogane, Haiti. We aim to recruit a total sample of 200 women.

Inclusion criteria for research participants include adults over 18 years old who are: capable of providing informed consent; living in an internally displaced persons camp; interested in attending the 6-week program of women’s health discussions; interested in conducting a post-test survey.

**Peer health workers** will include 8 women living in IDP camps in Leogane, Haiti who have high rates of literacy in oral and written Haitian Creole and experience conducting research and/or educational activities. [name], program development advisor at NEGES Foundation, will identify women interested in being hired as peer health workers (PHW). PHW will be supervised by the study coordinator based at NEGES and [name].

**5.3 Study components**

There are 6 components to the overall project:

(1) developing a survey to assess outcomes (HIV/STI knowledge and risk factors, trauma, depression, resilient coping, social support, relationship power)

(2) developing a peer health worker training manual and HIV educational videos

(3) training women in IDP camps in Leogane, Haiti to be peer health workers (PHW)

(4) conducting tablet-based pre-test and post-test surveys to collect information on outcomes among women living in IDP camps in Leogane, Haiti

(5) conducting 6 weekly sessions with women living in IDP camps in Leogane, Haiti

(6) conducting a community forum including women living in IDP camps to share basic HIV/STI information and to disseminate findings from the project

**5.3.1 Activities:**

***(1) Developing a survey to assess outcome measures/goals***

Previous literature, outlined in the Introduction section, has highlighted high rates of HIV and STI and low HIV/STI knowledge among women in Haiti. The survey will be based on pre-existing scales with established reliability and validity (*described in ‘outcome measures’ section below*) will be translated into Haitian Creole. We will hold two focus groups to pilot test scales. Focus groups will be held with: service providers (n=1) and peer health workers (n=1) in Leogane, Haiti to assess outcome measures. Each focus group will include 6-10 participants, will be conducted in Haitian Creole, transcribed, translated into English and analyzed using thematic analysis (Braun & Clark, 2006). Focus groups will involve reviewing each outcome measure for its cultural, gender and contextual relevance for women in Leogane. Surveys will be modified based on focus group feedback to ensure culture, gender and context appropriateness. Participation in pilot testing will be voluntary. There will be no repercussions for those people who choose not to pilot test the tool. This feedback will be integrated into the development of the final survey. Results from pilot testing will not be included in data analysis and surveys will be destroyed immediately.

***(2) Develop a training manual and educational video messages***

A training manual will be developed for the PHW: this training manual will include discussion points, information, and activities to guide each of the weekly women’s health meetings. The training will be primarily based on the Population Council’s ‘It’s All ONE Curriculum: A Unified Approach to Sexuality, Gender, HIV and Human Rights Education’ (http://www.popcouncil.org/publications/books/2010_ItsAllOne_Who.asp). The ‘It's All One Curriculum’ is designed primarily for community educators responsible for education in the areas of sexuality/sexual health. The Population Council describes with this curriculum: *“Users may draw on the guidelines and activities in this kit to meet their needs, for example: to develop or modify comprehensive curricula (of any duration) appropriate for their setting; to design more narrowly focused teaching units (for example, on gender or sexual health); and to use as a resource for single-topic lesson plans (for example, gender and the media, deciding about sex, protecting oneself and one’s partners from HIV, reflecting on masculinity).”* (Downloaded from: http://www.popcouncil.org/publications/books/2010_ItsAllOne_Who.asp)

This curriculum has been developed cross-culturally and provides case studies from around the world and provides guidance on how to adapt the materials for use in different contexts. The PI, co-investigator and coordinator will work collaboratively to ensure the sections developed for use in the training manual for this research project are culturally and gender relevant for women living in IDP camp settings in Leogane. Content areas for ‘It's All One Curriculum’ include: sexual health and well-being; gender; sexuality; interpersonal relationships; communication and decision-making skills; sexual and reproductive health.

***(3) Train peer health workers***

Peer health workers (PHW) will be considered employees and paid a rate equivalent to the hourly wage paid by the NEGES ($5/hour CAD; hired for 6 months for November to May at 20 hours/week). We will hire between 8-10 PHW who will be hired for training, participant recruitment, pre/post-test survey administration, and facilitation of weekly women’s health meetings. We will provide PHW with phone cards as needed to use for the duration of recruitment, survey implementation and weekly meetings. These phone numbers can be used by potential participants to contact the PHW, and for the PHW to contact the coordinator who will be based out of NEGES.

PHW will be considered members of the research team and their feedback and recommendations will guide recruitment strategies and survey implementation. The PHW will also have the opportunity to provide feedback on the survey itself through pilot-testing during the training.

In collaboration with NEGES we will develop and deliver a 10-day (paid) training that will consist of 2 components. The first component (2 days) will include basic research training: study design; confidentiality; ethics; informed consent; recruitment; survey implementation; facilitation skills for weekly meetings.

The second component (4 days) will involve training the PHW in the content areas for the six weekly women’s health meetings:

1. sexual health: HIV/AIDS
2. sexual health: sexually transmitted infections
3. interpersonal relationships
4. communication and decision-making skills
5. mental health and well-being
6. coping skills and social support

Content areas will be largely based on Population Council’s ‘It’s All ONE Curriculum’ (<http://www.popcouncil.org/publications/books/2010_ItsAllOne_Who.asp>). The content, discussion questions and activities will be implemented with the PHW who will have a chance to ask any questions and discuss any concerns. We will train the PHW for each weekly health session topic.

We will have the training documents translated into Haitian Creole; the PI, co-investigator (CD) and coordinator in conjunction with a translator will conduct the training at a private room in NEGES in Haitian Creole. Team debriefing will be provided on a bi-weekly basis by the coordinator based at NEGES and as needed.

The study coordinator will be hired to assist in: recruiting the PHW, acquiring project space and materials, developing the survey, recruiting participants, training the PHW, supervising community health workers, managing data collection, communicating with principal investigator and co-investigator, organizing the community forum, and co-facilitating the weekly women's health meetings at NEGES. The study coordinator will be based in Leogane, fluent in both English and Haitian Creole, familiar with Leogane and local community agencies, and experienced in supervising staff. The coordinator will be hired as part of the study team and paid $15/hour to work 20 hours/week for the study duration (18 months).

***(4) Conduct pre-test and post-test survey***

We will use a cross-sectional structured survey programmed on a tablet verbally administered by peer health workers. Eight peer health workers (PHW) will be hired: each PHW will administer the pre/post test to 25 participants. Benefits of verbally administered surveys include: enhancing accessibility to participants with differing levels of literacy; building trust between the interviewer and participant; and higher response rates (Mertens, 2005). I will provide training and written instructions to standardize and manualize the structured interviews. At the beginning of the interview the PHW will describe the sections that will be covered. Due to the sensitive nature of the topic (e.g. sexual risk factors) participants will be informed that they have the option to fill out the tablet-based survey (either the entire survey, or certain sections) independently if they wish and the peer health worker (PHW) will guide the participant on which button on the tablet to press to respond (e.g. top, middle, bottom) and will be present to answer any questions. It will be stressed to participants that their decision to participate is voluntary and they can withdraw from the study at any time. Participants can also skip questions or entire sections.

Following completion of the tablet-based survey, the tablet will be programmed to have an HIV/AIDS educational brief video (in Haitian Creole) on the tablet. The participant and PHW can watch the brief video (focused on HIV/STI education and prevention) together and the PHW will answer any questions the participant may have. Watching the video is optional and voluntary and the participant will be informed of this at the beginning of the survey and after completing the survey. Participants will be provided with an honorarium for the pre-test and post-test (equivalent to $5 CAD for each test). Participants will still be paid the full honorarium if they decide to not fully complete the survey or to leave when the survey is partially complete.

Surveys will be implemented in a private room within NEGES, an agency which participants are familiar with and many already attain services. Multiple strategies will be employed to protect confidentiality of participants. The PHW will be trained and 1) a significant part of the training will be regarding confidentiality and ethics and 2) the PHW will sign confidentiality agreements to protect confidentially of participants. No names or other identifying information will be collected on surveys or informed consent sheets, and informed consent sheets and surveys will be kept at a locked filing cabinet in NEGES. The surveys will have an ID number so pre and post-test scores can be compared. A sheet with the ID number and participants first name and last initial will be kept in a locked filing cabinet at NEGES; PHW will only have access to this sheet during data collection. Participants will also have an option to keep an informed consent sheet, which will be evidence of survey participation, or to have access to it at NEGES. Signatures will not be required for the informed consent; to enhance confidentiality participants can sign with an X.

***(5) Conducting weekly women’s health meetings***

Each PHW (n=8) will conduct a 2-hour women’s health meeting at NEGES once a week for 6 weeks. Meetings will be held when NEGES is closed and each PHW will conduct meetings at different times: this will help to ensure privacy. Each PHW will carry out the 6 meetings with the 25 women they conducted the pre test with. Participants will receive an honorarium for each session attended and food and refreshments will be provided. PHW will have a training manual with the outline for each session, including: learning points, a case study, activities and discussion questions. Each session will begin with ground-rules and discussions about confidentiality (e.g. importance of not sharing individual’s comments from the discussion outside of the meeting).

Weekly meetings will address: (1) sexual health: HIV/AIDS; (2) sexual health: sexually transmitted infections; (3) interpersonal relationships; (4) communication and decision-making skills; (5) mental health and well-being; (6) coping skills. Limits of confidentiality will also be discussed with participants, in particular participants will learn that confidentiality cannot be guaranteed during group meetings and to keep this in mind when they are sharing personal information. Sessions will be conducted in Haitian Creole, and PHW will record notes following each session regarding any questions or points that need clarification. The coordinator will meet with the PHW weekly to provide support, clarification and any guidance requested.

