**5.6** **Participant Recruitment**

**5.6.1 Sample Size Justification**

This study will aim to recruit 200 participants. There are 7 outcome variables, and a minimum sample size of 20 participants per variable is recommended for MANOVA (Field, 2009). Due to the possibility of attrition in this population we will aim to recruit 200 participants although 160 would be the minimum sample size required to detect a significant effect.

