**5.6.2** **Sampling Methods**

Survey participants will be recruited through trained peer health workers (PHW) hired for the research study as well as a study coordinator hired and based at NEGES community development agency. Purposive sampling methods will be used, specifically a) venue-based and b) peer-driven recruitment. Many potential participants are illiterate and do not have telephones; thus no recruitment will be done from participants’ homes and no flyers or print advertising will be used.

**Peer-driven Recruitment:** PHW will verbally disseminate information about the study and invite eligible participants, using a peer driven recruitment (PDR) technique. Peer driven sampling techniques are a component of participatory action research and involve: direct contact between the PHW and the participant, recruitment from social networks, and regulating the number of participants each PHW can recruit (Magnani, 2005). For this research project, each PHW can recruit a maximum of 25 participants. Peer to peer recruiting has been found to be an effective strategy to engage marginalized and stigmatized populations in HIV research and has been found to have positive effects with regard to informal peer education, health promotion and sharing of HIV resources (Tiffany, 2006). PDR can also be used to disseminate research findings back to marginalized populations.

As described by Tiffany (2006), we will follow the steps of PDR: 1) engaging stakeholders (i.e. NEGES) in planning this research, 2) engaging with PHW recommended by community organizations (e.g. NEGES, 3) involving PHW in planning the recruitment strategy and pilot testing the survey, 4) employing PHW to recruit participants who may then choose to inform people within their social networks of the study. Special care is taken in the PHW training to explain informed consent, confidentiality and voluntary participation to PHW due to this sampling technique. PHW will sign confidentiality agreements. The peer driven recruitment approach “to recruiting members of hidden, vulnerable and marginalized populations to participate in research projects can contribute to more inclusive community dialogue about social issues and strengthen community participation in research efforts” (Tiffany, 2006, p. 122).

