**5.8.2 MANOVA Analyses**

Multivariate analysis of variance (MANOVA) will be used to assess pre and post-test differences across outcome variables. Separate MANOVA analyses will be conducted for primary outcome variables focused on HIV/STI (HIV knowledge, STI knowledge, HIV/STI risk factors, relationship power) and secondary outcome variables focused on mental health (depression, trauma, resilient coping, social support). We will compare differences in participant scores from the pre-test and post-test (after the 6-weekly health meetings) to assess if the intervention influenced any of the primary or secondary outcomes. We will conduct a multivariate analysis of covariance (MANCOVA) to control for the number of weekly health meetings attended. Significant MANCOVA will be followed up with both univariate tests and discriminant function analyses (DFA) to understand significant effects. DFA can be used to identify variates (combinations of dependent variables) and how the dependent variables contribute to the variates. Analyses will be conducted using SPSS 19 software.

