4. The Beck Depression Inventory –Fast Screen (BDI-FS) will be used, however only 6 items will be used. The item on suicidality will not be included as PHW may not feel adequately trained to cope effectively with a suicidal participant and may not have the resources to provide appropriate crisis management.

5. Participants will be provided with a list of community resources, including community health and mental health agencies and government run clinics. Participants will also be provided a contact number for NEGES of an individual who can provide support and services who is not a member of the research team. Participating or not in the study in no way affects access to services at NEGES or any other community agency.

**Social risks** include loss of privacy and breaches of confidentiality regarding self-disclosed personal information in the *tablet-based pre/post-test survey*. In order to minimize above risks associated with confidentiality:

1. No participant names will be collected and participants will be asked to mark X on the consent form to indicate their consent. This X will be used to ensure confidentiality. No identifying information will be collected (i.e. no full names, no date of birth).

2. Participants have the option to take a copy of the informed consent form, which will be the only evidence linking them to the study, or to view it when/if they choose by going to NEGES where there will be a copy of the informed consent available to view.

3. PHW trained in research and confidentiality issues will work on an individual basis with participants to administer the tablet-based surveys. Participants, regardless of literacy, will be supported and guided to fill out the tablet-based survey independently to maintain privacy if they wish.

4. PHW will be well trained in research ethics and interviewing techniques with special attention paid to confidentiality. PHW will also sign confidentiality agreements.

5. PHW will be assigned to work with participants who they do not have a personal or professional relationship with. The study coordinator will inform the participant that she can choose to work with a different PHW who she may have been assigned to work with for the pre/post test and the intervention.

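### The analysis has no term for peer health worker group, and the sample size no allowance for it, although each of eight workers surveys and teaches her own 25 women

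*Protocol*

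**What the plan says.** Section 5.3.1 (4) sets up the surveys by PHW: "Eight peer health workers (PHW) will be hired: each PHW will administer the pre/post test to 25 participants". Section 5.3.1 (5) gives the same women to the same PHW for the intervention, six weekly two-hour group meetings: "Each PHW will carry out the 6 meetings with the 25 women they conducted the pre test with". Section 7.1 lets a woman move: "she can choose to work with a different PHW who she may have been assigned to work with", and the same section offers a change of discussion group.

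Section 5.8.2 fixes the analysis: "Multivariate analysis of variance (MANOVA) will be used to assess pre and post-test differences across outcome variables". A MANCOVA follows, with the number of meetings attended as its only named covariate. A significant result leads to univariate tests and discriminant function analysis. Neither PHW nor group is mentioned.

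Section 5.6.1 bases the sample size on a count of variables: "There are 7 outcome variables, and a minimum sample size of 20 participants per variable is recommended for MANOVA". It then states that "160 would be the minimum sample size required to detect a significant effect", with 200 to be recruited to cover attrition. It gives no ICC, effect size, standard deviation, significance level or power.

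**The concern.** A skilled facilitator, a lively group or a leading interviewer moves the scores of all the women in that group together. The facilitator and the group act between the two surveys, so they affect the change itself, and subtracting the pre-test score does not remove them. The analysis then counts up to 200 separate pieces of evidence on the average change, while the variation between facilitators is seen only eight times.

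At stake is the main result. If the correlation is ignored, the standard error of the mean change in HIV knowledge and in each secondary outcome is too small, the intervals are too narrow, and a change is declared significant too often. Adjusting for meetings attended does not cure this, because attendance is a characteristic of the woman and does not represent what her group shares.

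**Working it through.** **Inputs from the protocol.** 8 PHWs and 25 women each (5.3.1 (4) and (5)), so 8 × 25 = 200. The stated minimum is 160 (5.6.1), or 20 per PHW if losses are even. Section 5.3.1 (3) speaks of hiring 8 to 10 PHWs; 8 is used here because the survey and meeting sections both use it.

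**Assumed inputs.** The ICC of the change scores (0.01, 0.02, 0.05, 0.10) and, in the last step only, the correlation between a woman's two scores (0.5). The protocol gives neither.

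**The plan's own figure.** The stated rule gives 7 × 20 = 140, not 160; 8 × 20 = 160 would match. The target follows from either 160 / 0.80 = 200 or 8 × 25 = 200. No reading contains a clustering term. The gap between 140 and 160 is a separate matter.

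**Effect of the PHW groups on a paired analysis.**

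- Design effect: DE = 1 + (m − 1) × ICC, with m the number of women per group.
- Effective sample size: N / DE.
- The standard error is too small by a factor of √DE.
- Actual error rate of a nominal two-sided 5% test: 2 × [1 − Φ(1.96 / √DE)].

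Worked case, m = 25 and ICC = 0.05: DE = 1 + 24 × 0.05 = 2.20; effective n = 200 / 2.20 = 91; √2.20 = 1.48; error rate = 2 × [1 − Φ(1.96 / 1.48)] = 0.186.

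| Assumed ICC of change | 0.01 | 0.02 | 0.05 | 0.10 |
|---|---|---|---|---|
| **8 × 25 = 200:** design effect | 1.24 | 1.48 | 2.20 | 3.40 |
| Effective n | 161 | 135 | 91 | 59 |
| Actual type I error | 0.078 | 0.107 | 0.186 | 0.288 |
| **8 × 20 = 160:** design effect | 1.19 | 1.38 | 1.95 | 2.90 |
| Effective n | 134 | 116 | 82 | 55 |
| Actual type I error | 0.072 | 0.095 | 0.160 | 0.250 |

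Simulating the paired t test agrees with the 8 × 25 row to within about 0.2 percentage points. From ICC 0.02 upwards, all 200 women carry less information than 160 independent ones. Reaching 160 effective observations with groups of 25 would need 160 × DE = 199 / 237 / 352 / 544 women.

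**Degrees of freedom.** With eight groups a group-level test has 8 − 1 = 7 degrees of freedom. Its critical value is 2.36, against 1.97 when women are counted singly.

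**If the pairing were ignored as well.** The ratio of true to reported standard error becomes √[(1 − ρ) × DE], where ρ is the pre/post correlation. With 160 women and ρ = 0.5, at ICC 0.05 this is √(0.5 × 1.95) = 0.99 and the error rate is 0.047. At ICC 0.01 it is 0.011, and at 0.10 it is 0.104. The two errors pull in opposite directions, so the figures in the table apply only to a paired analysis.

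**The case against.** **The ICC may be small.** The protocol standardises interviews with training and written instructions, supplies a session manual, has the coordinator support the PHWs, and lets women complete the survey themselves. All of this limits differences between PHWs. The objection stands as a reason to show a range starting at 0.01, but even there the test runs at about 8%. A shared recruiter adds little to the argument: "each PHW can recruit a maximum of 25 participants" only caps recruitment, the coordinator also recruits, and sections 5.6.2 and 7.1 steer women away from PHWs they know. The shared interviewer, facilitator and discussion group remain.

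**The SAP, or the analyst, could add a PHW term.** It could, and each PHW has her own tablet and USB key, so the grouping may be recoverable. But section 5.8.2 already names the model, the covariate and the follow-up tests, and the sample size is fixed without any allowance. A tablet also shows who ran the survey, not which group a woman attended after a switch.

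**Generalisation depends on the question.** If interest is confined to these eight PHWs, they could be treated as fixed. The protocol does not confine it: section 2 presents the study as a model that could inform other camps.

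**A stronger reading is tempting.** A reader might infer that each woman's two scores are analysed as if they came from different women. No repeated-measures form is named, section 5.1 calls the baseline scores the control group, and discriminant analysis needs groups. The documents do not support that inference. The protocol nowhere states that the two scores are independent. ID numbers link the surveys, 5.8.2 speaks of comparing differences in participants' scores, and the women serve as their own control. These point to a within-woman comparison whose form is left unstated. Nor may the losses from ignoring both features be added together, as the last step of the working shows.

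**Conclusion.** The concern holds for the PHW groups. The design creates eight groups that share interviewer, facilitator and discussion; neither the analysis nor the sample size recognises them. A paired analysis of individual women would understate the standard error of the change by a factor of about 1.11 / 1.22 / 1.48 / 1.84 at ICC 0.01 / 0.02 / 0.05 / 0.10. The size rests on an ICC that the protocol does not give, on equal groups and on pairing; the direction needs only an ICC above zero, which is likely here but not documented.

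On pairing, the protocol needs a clarification and does not contain a demonstrated error. The discriminant step is the one part that would misfit: with pre and post as its two groups, it would treat each woman's two scores as separate cases.

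**What to change.** **Section 5.8.2.** Analyse within-woman change in HIV knowledge, and in each secondary outcome, with PHW group as the cluster. An equivalent is a linear mixed model with time as the fixed effect, a random intercept for woman and a random PHW-group effect on the change. Use Satterthwaite or Kenward-Roger degrees of freedom (about 7). Confirm with a one-sample t test on the eight group mean changes (7 degrees of freedom). HIV knowledge is the single primary outcome in 5.4 and should carry the main test; say how multiplicity across the secondary outcomes is handled, since separate models replace the joint test.

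**Dataset.** Carry the PHW identifier and the group actually attended into the analysis file, because women may switch. Do this before the linking sheet is destroyed after the post-test (5.7).

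**Section 5.6.1.** State an assumed ICC and what 8 × 25 women can detect under it.

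**Clarification.** State that the pre/post comparison is paired. Drop the discriminant analysis, or run it only descriptively on change scores.

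**Cost.** Analysis wording and two stored variables; recruitment and delivery are unchanged. Confidence intervals widen by √DE × 2.36 / 1.97, about 1.3 / 1.5 / 1.8 / 2.2 times at the four ICCs with 200 women, and power falls accordingly.
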